### Study Procedure

Figure 1 shows the CONSORT (Consolidated Standards of Reporting Trials)–based RCT flow diagram depicting the enrollment of participants for each phase of the study: randomization, follow-up, and endline assessment. Table 1 depicts the timeline of the trial activities.

**Figure 1 figure1:**
[figure not shown]
RCT CONSORT flow diagram for recruitment, follow-up, and endline assessment of participants in the study. CBC: complete blood count; CONSORT: Consolidated Standards of Reporting Trials; DST: drug susceptibility testing; ESR: erythrocyte sedimentation rate; FGD: focus group discussion; hs-CRP: high-sensitivity C-reactive protein; IDI: in-depth interview; RCT: randomized controlled trial; SAM: severe acute malnutrition.

**Table 1 table1:** Timepoints and activities to be carried out during the study.

Activity	Baseline	Enrollment to RCT^a^ (within 7 days of collecting baseline data)	Telephonic follow-up at 15, 45, 75, and 105 days (plus 5 days allowed at each timepoint)	Physical follow-up at 30, 60, 90, 120, and 180 days (plus 5 days allowed at each timepoint)
Consent; appetite test; sociodemographic, nutritional, and health-related information obtained through questionnaires during face-to-face interviews + 4 mL^b^ of blood sample, urine sample, and stool sample for CBC^c^, ESR^d^, culture, DST^e^, hs-CRP^f^, procalcitonin, and anthropometry (height, weight, MUAC^g^)	✓	—^h^	—	—
RCT eligibility assessment, randomization and antibiotic distribution, and IFA^i^ syrup distribution in the case of anemia	—	✓	—	—
Weight, height, MUAC, symptoms of adverse events, any illness, and treatment details	—	—	—	✓
Symptoms of adverse events, any illness, and treatment details	—	—	✓	✓

^a^RCT: randomized controlled trial.

^b^Biological samples will be collected from 606 study participants.

^c^CBC: complete blood count.

^d^ESR: erythrocyte sedimentation rate.

^e^DST: drug susceptibility testing.

^f^hs-CRP: high-sensitivity C-reactive protein.

^g^MUAC: mid-upper arm circumference.

^h^Not applicable.

^i^IFA: iron folic acid.

#### Phase 1

A list of children with uncomplicated SAM will be obtained from the NHTS website through district stakeholders. The children will be visited at their homes to confirm their diagnosis and malnutrition category and will be enrolled into the study after obtaining informed consent from the caregivers. The children’s sociodemographic, nutritional, and health-related information will be obtained through questionnaires and interviews. Under a sterile environment, 4 mL of blood sample will be taken from each child. Two sterile containers will be given to the children to collect urine and stool samples, and those samples will be collected from the caregivers the following day.

Blood samples will be transported in 2-8^o^C and will be sent to the biochemistry laboratory within 4 hours of sample collection. The samples will be analyzed in the biochemistry (high-sensitivity C-reactive protein [hs-CRP], procalcitonin) and pathology (complete blood count [CBC], erythrocyte sedimentation rate [ESR], and white blood cell [WBC] count) laboratories. Blood, stool, and urine samples will be analyzed in the microbiology laboratory for culture and sensitivity, and urine samples will additionally be analyzed for complete urine examination in the pathology laboratory. To capture the mental health status of both parents, consent from both will be obtained.

#### Phase 2

FGD and IDI guides (Multimedia Appendices 1 and 2) will be prepared based on the literature review and the knowledge gap requiring further data [39]. Potential participants for qualitative interviews will be identified and appointments will be made. A moderator trained in qualitative research will conduct the FDGs and IDIs. The date and time of the FGDs and IDIs will be fixed at the participants’ convenience. On the day of the FGDs and IDIs, informed consent will be obtained, and the entire process will be audio-recorded. An assistant will take field notes, and a sociogram will be used to map the participation pattern. Participatory rural appraisal techniques will be used to encourage active participation and generate more discussion among the participants in the FGDs. The duration of each FGD and IDI will be 30-45 minutes.

#### Phase 3

A list of children with uncomplicated SAM will be obtained from the NHTS website. The children will be visited at their homes to confirm their nutritional category. At enrollment, each child will be assigned a unique identification number based on the number in the list. After baseline assessment, children will be randomized using stratified randomization to one of three groups: amoxicillin (5 days, twice a day, 15 mg/kg based on weight band + standard nutritional care), azithromycin (single dose, 20 mg/kg + standard nutritional care), or control (no antibiotics + standard nutritional care). Children with subclinical infection will be randomized to either the amoxicillin or the azithromycin group in a 1:1 allocation ratio. Children without any subclinical infection will be randomized to the amoxicillin, azithromycin, or control group in a 1:1:2 randomization sequence to balance the stratified randomization based on subclinical infection status. The remaining children who will be assessed clinically for uncomplicated SAM, who pass the appetite test, and who are found eligible will be assigned to one of the three groups in a 1:1:1 randomization sequence; these children will be recruited after completion of the phase 1 enrollment. Around 150-200 participants are expected to be recruited after phase 1 enrollment to fulfill the sample size requirement for phase 3.

Three separate randomization sequences of unequal block sizes will be generated. A non–peer-reviewed study [40] from Bangladesh reported that 36% of children with uncomplicated SAM have elevated CRP and α1-glycoprotein. Assuming that 35% of children with uncomplicated SAM might have a subclinical infection [40], a randomization sequence will be generated using online software. The allocation will be concealed centrally in the institute. Based on the intervention plan, study participants and administrators will not be masked in the study.

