**Objective:**

This study aims to (1) estimate the prevalence of clinical/subclinical infections and describe AMR patterns among children aged 6-59 months with uncomplicated SAM and assess associations with sociodemographic, clinical, and nutritional factors; (2) explore health-seeking behavior, antibiotic use, and care preferences among caregivers and health care providers; and (3) evaluate the efficacy of 7-day amoxicillin versus single-dose azithromycin versus no antibiotics in weight gain and nutritional recovery among children with SAM.

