**Methods:**

This mixed methods study will be part of the ongoing CSAM program implemented in selected districts of Telangana, India. Phase 1 will be a cross-sectional analytical study with a laboratory component to estimate the prevalence of clinical/subclinical infections and AMR among 606 children. Phase 2 will use a qualitative design (focus group discussions with caregivers and in-depth interviews with health care providers) to explore perceptions and practices related to management and antibiotic use among the children. Phase 3 will be an open-label, parallel-group randomized controlled trial (RCT) with three groups of ~250 children each to compare nutritional recovery: 7 days of amoxicillin + standard nutritional care, single-dose azithromycin + standard nutritional care, and no antibiotics + standard nutritional care (control). Children will be followed for up to 6 months, with periodic anthropometric, clinical, and laboratory assessments.

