An RCT [34] conducted in Kanpur, India, among 100 children with uncomplicated SAM (amoxicillin vs placebo) reported no significant differences in clinical or anthropometric parameters between groups. A systematic review and meta-analysis [24] similarly reported that the evidence on empirical antibiotic usage among children with uncomplicated SAM is weak and may require urgent testing.

The Indian Council of Medical Research’s (ICMR) 2019 “Treatment Guidelines for Antimicrobial Use in Common Syndromes” recommend empirical antibiotic use in common illnesses, such as severe sepsis and septic shock, acute bacterial meningitis, community-acquired pneumonia, and necrotizing fasciitis, only when proven to be beneficial. The guidelines also suggest de-escalating or modifying therapy based on culture and drug susceptibility [35]. There is evidence of acute respiratory infection (ARI; 50%) [36] and diarrhea from the NFHS-5 (7.3%), ARI from the NFHS-5 (2.8%), and fever or ARI from the NFHS-5 (69%) [3]. However, there is no evidence in community-based studies of confirmed bacterial infection among children, and most infections among children aged <5 years are suspected to be of viral origin. A 2004 Lancet review [37] reported that the coverage offered by the aminopenicillins group of antibiotics is only 37% in the case of pediatric sepsis in Southeast Asia and the Pacific region [37].

Considering all this evidence, the rationale behind using empirical antibiotics requires urgent assessment, and there is a dire need for a control arm without antibiotics to assess the efficacy of empirical antibiotics in children with uncomplicated SAM. Therefore, this study aims to (1) estimate the clinical/subclinical infection and AMR patterns among children with uncomplicated SAM; (2) explore health-seeking behavior, antibiotic use, and care preferences among caregivers of pediatric patients and identify challenges and facilitators faced by health care providers in patient management; and (3) compare the effectiveness of single-dose azithromycin, 5-day amoxicillin, and no antibiotic therapy on nutritional recovery and clinical outcomes.

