### Intervention Phase

Following eligibility testing, children will be enrolled in one of the three groups based on stratified randomization. Baseline data of various independent and dependent variables will be captured for each child with proper screening of anthropometric measures and medical assessment. Next, each child will receive either oral amoxicillin or azithromycin and standard nutritional care (Balamrutham Plus) based on the group. In addition, based on the hemoglobin level, children with anemia at baseline will be administered iron folic acid (IFA) syrup as per Anemia Mukt Bharat guidelines [41]. Any illness during the intervention period, physician (or pediatrician) visits, treatment details, and hospitalization details will be documented during the follow-up visits.

In the amoxicillin group, amoxicillin dispersible tablet (125 mg) will be administered, along with Balamrutham Plus. The first dose will be administered upon enrollment, following by medication at home (for 5 days, twice daily). The dosage will be determined based on weight of the child, as specified by the SSFP implemented by the Government of Telangana for managing children with SAM in all districts of Telangana (Table 2) [20].

**Table 2 table2:** Dosage of amoxicillin dispersible tablets.

Weight of child (kg)	Prescription	Tablets required, n
4.0-6.9	1 tablet twice daily for 5 days	10
7.0-9.9	1.5 tablets twice daily for 5 days	15
10.0-12.9	2 tablets twice daily for 5 days	20
13.0-15.9	2.5 tablets twice daily for 5 days	25
16.0-18.9	2.5 tablets twice daily for 5 days	25

In the azithromycin group, a single dose of azithromycin syrup (20 mg/kg) will be administered, along with Balamrutham Plus.

In the control group, no antibiotics will be prescribed; only standard nutritional treatment (Balamrutham Plus) will be provided.

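### The amoxicillin arm is described as 7 days in the abstract and primary objective but 5 days in the procedures, and the stated 15 mg/kg matches no weight in the dosing table

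*Protocol article*

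**What the plan says.** The Protocol article states the length of the amoxicillin course in several places.

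- **Seven days.** The abstract's Objective is to "evaluate the efficacy of 7-day amoxicillin versus single-dose azithromycin versus no antibiotics". The abstract's Methods lists the arm as "7 days of amoxicillin + standard nutritional care". The third primary objective under Study Objectives also names a 7-day course, and the abstract's Background gives 7 days as its example amoxicillin regimen.
- **Five days.** The aims at the end of Need for a Control Group With No Antibiotics are to "compare the effectiveness of single-dose azithromycin, 5-day amoxicillin, and no antibiotic therapy". Study Procedure, Phase 3 defines the randomised arm as "amoxicillin (5 days, twice a day, 15 mg/kg based on weight band + standard nutritional care". Intervention Phase has the first dose given at enrolment, "following by medication at home (for 5 days, twice daily"). All five rows of Table 2 are for 5 days, for example "2.5 tablets twice daily for 5 days".

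The dose is also stated twice. Study Procedure, Phase 3 gives 15 mg/kg by weight band, twice a day. Intervention Phase says that an "amoxicillin dispersible tablet (125 mg) will be administered", with the number of tablets set by the state programme's weight table (Table 2). No section reconciles either pair of statements.

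**The concern.** The objective and the procedures name different courses for the same arm. Need for a Control Group and Study Objectives are adjacent sections and state the same aim with different durations. Rationale of the Study and Study Area describe existing programme care as amoxicillin twice daily for 5 days, so the choice of label decides whether the trial is seen to test current care or a different course.

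Three things depend on it. A result reported under the stated objective could describe a course that Table 2 does not deliver, and the authors intend the findings to inform national guidelines. Compliance is judged from empty amoxicillin strips collected at 30 days (Follow-Up Visits), which needs one prescribed quantity as its denominator. A per-protocol analysis is planned (Data Entry and Analysis, Phase 3), and it needs one prescribed course to be judged against.

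The dose mismatch adds a second ambiguity: a reader who takes 15 mg/kg from the arm definition would misstate the exposure that Table 2 produces.

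**Working it through.** **Inputs.** From Intervention Phase and Table 2: tablet strength 125 mg; two doses a day; tablets per dose 1, 1.5, 2, 2.5 and 2.5 across the five weight bands; tablets required 10, 15, 20, 25 and 25. From Study Procedure, Phase 3: 15 mg/kg.

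**Duration.** Tablets required = tablets per dose × 2 × days.

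- 5 days: 1×10, 1.5×10, 2×10, 2.5×10, 2.5×10 = 10, 15, 20, 25, 25. This reproduces the Table 2 column exactly.
- 7 days: 1×14, 1.5×14, 2×14, 2.5×14, 2.5×14 = 14, 21, 28, 35, 35. No row agrees.

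Table 2 is therefore consistent only with 5 days. Doses per course are 2 × 5 = 10. A 7-day course would have 2 × 7 = 14 only if it too were twice daily; the 7-day statements give no frequency, so 14 is an assumption.

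**Dose.** mg/kg per dose = tablets per dose × 125 ÷ body weight, at the limits and midpoint of each band.

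| Band (kg) | mg per dose | At upper limit | At lower limit | At midpoint |
|---|---|---|---|---|
| 4.0–6.9 | 125 | 125/6.9 = 18.1 | 125/4.0 = 31.3 | 125/5.45 = 22.9 |
| 7.0–9.9 | 187.5 | 187.5/9.9 = 18.9 | 187.5/7.0 = 26.8 | 187.5/8.45 = 22.2 |
| 10.0–12.9 | 250 | 250/12.9 = 19.4 | 250/10.0 = 25.0 | 250/11.45 = 21.8 |
| 13.0–15.9 | 312.5 | 312.5/15.9 = 19.7 | 312.5/13.0 = 24.0 | 312.5/14.45 = 21.6 |
| 16.0–18.9 | 312.5 | 312.5/18.9 = 16.5 | 312.5/16.0 = 19.5 | 312.5/17.45 = 17.9 |

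The lowest value in the table is 16.5 mg/kg (at 18.9 kg) and the highest 31.3 mg/kg (at 4.0 kg). The stated 15 mg/kg lies below the whole range of every band. Reading it as a daily dose widens the gap: doubling gives 33.1 to 62.5 mg/kg per day.

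**Most favourable reading.** Suppose 15 mg/kg is a minimum, rounded up to the next half tablet at the top of each band. The exact requirements, 15 × upper limit ÷ 125, are 0.83, 1.19, 1.55, 1.91 and 2.27 tablets, which round up to 1, 1.5, 2, 2 and 2.5. This matches Table 2 in four bands but not at 13.0–15.9 kg, where the table has 2.5. The article states no such rule, and even under it every child in the table would receive more than 15 mg/kg.

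**The case against.** The strongest reply is that the arm is specified well enough to run. Every section that tells staff what to give (the Phase 3 procedure, the Intervention Phase text and all of Table 2) agrees on 5 days. Table 2 states the tablets per child, and Intervention Phase names that table as the source of the dosage. Drug supply and the strip count could follow from it, so the 7-day wording may be only a conflicting label, and the per-protocol definition is normally left to a fuller document.

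Much of this stands. A reader might infer that the arm is undefined, or that the trial's comparator is. The document does not support that: the arm is inconsistently defined, and amoxicillin is one of two intervention arms, the control being no antibiotic. But agreement among the operational sections does not remove a different course from the primary objective, nor does it settle which text is right.

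On dose, weight bands always round, and the largest excess (31.3 against 15, or 108%) applies only to a child of exactly 4.0 kg. At midpoints the excess is about 19% (17.9/15) to 53% (22.9/15). That is a fairer summary, but ordinary rounding would put the nominal dose somewhere inside the bands, and here it lies below all five.

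A reader might also take the identical prescription in the two top bands as a mistake. Nothing in the article says that the tablet number must rise with every band, and the table is attributed to a programme source that is not shown. It is not demonstrated to be an error.

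**Conclusion.** The contradiction holds as written and should be corrected before randomisation. The duration is 7 days in the abstract and primary objective and 5 days in the aims, procedures and Table 2. That is 10 doses against 14 if both courses are twice daily, which is assumed for the 7-day course. The stated 15 mg/kg is received at no weight in Table 2, where doses run from 16.5 to 31.3 mg/kg, or about 18 to 23 mg/kg at band midpoints. The duration conflict is the more serious because it reaches the primary objective; the dose mismatch is secondary.

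A reader might infer that the registered objective is also wrong. The article gives only a registration number, so the entry's wording is unknown and this is a matter to check. No sample-size figure depends on this point.

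**What to change.** Before the RCT randomises:

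1. Reconcile the abstract (Background, Objective, Methods), the aims in Need for a Control Group With No Antibiotics, Study Objectives, Study Procedure Phase 3, and Intervention Phase with Table 2 to one duration.
2. Reconcile the mg/kg statement with Table 2, treating neither as governing in advance. If a rounding rule links them, state it. Which duration or dose is right is for the investigators to decide.
3. Use the same arm description in the objective, procedures, adherence measure and per-protocol definition, and confirm that the registry entry agrees.
4. As a courtesy check, confirm the repeated prescription in the two top weight bands against the programme source.

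The cost is a text correction plus notice to the ethics committee and the registry, which Ethical Considerations already provides for. Aligning the texts needs no change to the trial's design. The Results section reports that the RCT component is delayed while phases 1 and 2 have begun, so the correction is cheap now and would be harder once children have been randomised.

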### Sample Size

#### Phase 1

Bhutta et al [8] reported that the rates of clinical infections among children with complicated SAM vary from 15% to 68%. Considering 50% prevalence of lower respiratory tract infection among children with uncomplicated SAM, 95% CIs, 10% relative precision, 1.5% design effect, 10% nonresponse rate, and 5% type I error, we will require 606 participants aged 6-59 months with uncomplicated SAM.

#### Phase 2

A purposive sampling strategy will be followed to select participants. Primary caregivers of children with uncomplicated SAM will be identified based on their volunteerism and participation. Yadadri Bhuvanagiri District comprises four project areas (Bhongiri, Aler, Mothkur, and Ramanapeta), each consisting of multiple sectors and each sector covering 25 *Anganwadi*s [38]. FGDs are planned at the project level to ensure adequate representation across geographic areas and variations in the distribution of children with uncomplicated SAM. Initially, two FGDs are planned per project area; however, considering the larger geographic coverage and higher caseload in two project areas, an additional FGDs will be conducted in each of these areas based on data flow. In total, 10-12 FGDs will be conducted to capture diversity in experiences and practices across the district. Each FGD will include 8-10 participants.

As the aim is also to explore barriers and facilitators related to the management of children with uncomplicated SAM, IDIs are planned to include service providers across different levels of the health system. This approach reflects the continuum of care, as a child with uncomplicated SAM encounters multiple providers at different points within the health system. Therefore, two IDIs will be conducted in each health care worker group: Accredited Social Health Activist (ASHA), *Anganwadi* teacher (center), ANM (subcenter), MO (PHC), and pediatrician (district hospital and tertiary care center).

The data saturation principle will guide the final number of FGDs and IDIs to be conducted. Saturation will be considered achieved when no new themes, patterns, or insights emerge from successive FGDs or IDIs and when there is redundancy in the information obtained. Data collection and analysis will be undertaken simultaneously to monitor saturation, and additional FGDs or IDIs will be conducted, if required.

#### Phase 3

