Data analysis will be performed in Stata version 18.0 software using intention-to-treat analysis at the end of the study. Per protocol analysis will also be performed as a secondary analysis at the end of the study. Interim analysis will be part of the quality parameter (at the end of the first year). The WHZ and MUAC will be expressed as mean (SD) or median (IQR) with 95% CIs based on data normality. The presence of bilateral pitting edema will be expressed as proportions with 95% CIs. Independent variables (child’s age in months and mother’s age) will be expressed as mean (SD) or median (IQR) with 95% CIs based on data normality. Factors such as education status, type of delivery, and birth complications will be expressed as proportions with 95% CIs. Outcomes such as episodes of acute illness, day care absenteeism, parenteral absenteeism, number of hospital visits, and food consumption will be expressed as mean (SD) or median (IQR) with 95% CIs based on data normality. Outcomes such as the presence of sepsis and mortality status will be expressed as proportions with 95% CIs. The chi-square test will be performed to analyze the association between outcomes and categorical independent variables. An unpaired *t* test (or Mann-Whitney *U* test) will be performed to assess the association between outcomes and continuous independent variables. Poisson regression analysis (bivariate and multivariate) will be conducted to explore the association between dependent and independent factors. Adjusted risk ratios with 95% CIs will be reported for factors included in the multivariate Poisson regression model.

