### Strengths and Limitations

In the Indian context, evidence is scarce for community-based management settings in which children with uncomplicated SAM are less likely to present with overt infections. Simultaneously, increasing AMR to commonly used antibiotics raises concerns about the continued empirical use of such drugs without clear benefits. This study is, therefore, expected to generate context-specific evidence to inform more rational and targeted use of antibiotics in the CSAM in the Indian context. The RCT design with three arms—amoxicillin, azithromycin, and no antibiotics—will allow for a comprehensive evaluation of both the effectiveness and the necessity of empirical antibiotic therapy, which is one of the major strengths of this study. Moreover, the study is embedded within a community-based management framework, enhancing its relevance to current national programs and real-world implementation. In addition, the inclusion of laboratory investigations to assess infection status and AMR provides a stronger evidence base that is often lacking in similar studies.

However, the study will be conducted within specific programmatic and geographic settings, which may limit generalizability to regions with differing infection burdens or health care access. Moreover, subclinical infections may not be fully captured due to inherent limitations in diagnostic methods. Operational challenges, such as timely collection and transportation of samples, particularly urine and stool samples among pediatric participants, may be difficult. In addition, adherence to treatment and follow-up in community settings may also influence study outcomes.

The findings of this study have important implications for both policy and practice. If empirical antibiotics are found to provide limited benefits in children with uncomplicated SAM, this could support revisiting existing guidelines and promoting more judicious use of antibiotics, in line with antimicrobial stewardship principles. However, if benefits are observed in specific subgroups, the study may help refine criteria for targeted antibiotic use.

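### Children with detected subclinical infection have no randomised control, so an antibiotic-versus-control comparison pooled over the three randomisation sequences would be confounded by infection status

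*Protocol article*

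**What the plan says.** Study Procedure, Phase 3, sets three randomisation sequences:

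- Detected subclinical infection: "Children with subclinical infection will be randomized to either the amoxicillin or the azithromycin group in a 1:1 allocation ratio".
- Tested, none detected: "Children without any subclinical infection will be randomized to the amoxicillin, azithromycin, or control group in a 1:1:2 randomization sequence".
- Later recruits, assessed clinically: they "will be assigned to one of the three groups in a 1:1:1 randomization sequence; these children will be recruited after completion of the phase 1" enrolment. Their number is given as follows: "Around 150-200 participants are expected to be recruited after phase 1 enrollment to fulfill the sample size requirement for phase 3".

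The text presents 1:1:2 as the means of balancing the stratified scheme. The prevalence behind it is also stated: "Assuming that 35% of children with uncomplicated SAM might have a subclinical infection". Footnote b of Table 1 limits biological samples to 606 participants.

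Data Entry and Analysis, Phase 3, plans intention-to-treat analysis, chi-square tests, unpaired t or Mann-Whitney tests, and regression: "Poisson regression analysis (bivariate and multivariate) will be conducted to explore the association between dependent and independent factors". It mentions neither randomisation sequence nor infection status.

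Study Objectives states the three-way comparison for all children aged 6-59 months with uncomplicated SAM. Strengths and Limitations adds that "if benefits are observed in specific subgroups, the study may help refine criteria for targeted antibiotic use".

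**The concern.** The probability of control is 0, 1/2 or 1/3 according to sequence, and sequence is defined partly by infection status. Randomisation protects the comparison within a sequence, not one that adds the sequences together. The protocol's own rationale for empirical antibiotics is that infection may hold back nutritional recovery, so infection status is a plausible predictor of the primary outcomes.

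Two things are at stake. First, a pooled antibiotic-versus-control contrast would mix the effect of the drug with the effect of being infected. Second, the sequence of children with detected infection carries no information on antibiotic versus none, although the objective makes no exception for them.

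**Working it through.** **Inputs.** From the protocol: the three allocation ratios, 35% infected and 150-200 later recruits (Study Procedure, Phase 3); 606 phase 1 children and 250 per arm (Sample Size); WHZ means -1.29 and -1.45 with SDs 0.84 and 0.93, 80% power, 480 per group (Sample Size, Phase 3). Assumed: every phase 1 child is randomised, later children have the same prevalence, and there is a WHZ gap between infected and uninfected children, shown as a range.

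**Step 1: the plan's own figure.** SD = √((0.84² + 0.93²)/2) = 0.886. n = 2 × (1.96 + 0.84)² × 0.886² / 0.16² ≈ 482 per group, so the stated 480 is reproduced. At 250 per arm, SE = 0.886 × √(2/250) = 0.079, and power = Φ(0.16/0.079 − 1.96) ≈ 52%.

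**Step 2: expected arms, 606 + 150 children, 35% infected.**

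| Sequence | Children | Amoxicillin | Azithromycin | Control |
|---|---|---|---|---|
| Infection detected, 1:1:0 | 212 | 106 | 106 | 0 |
| None detected, 1:1:2 | 394 | 98.5 | 98.5 | 197 |
| Later, 1:1:1 | 150 | 50 | 50 | 50 |
| Total | 756 | 254.5 | 254.5 | 247 |

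The sizes come out close to 250. They are exactly equal only if I/2 + U/4 = U/2 (I infected, U uninfected), that is, at one-third infected. At 10% infected they would be 217/217/323, and at 60% 292/292/171.

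**Step 3: composition.** Of the 50 later children in each arm, 35% (17.5) are infected but untested.

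- Antibiotic arm: (106 + 17.5)/254.5 = 48.5%.
- Control: 17.5/247 = 7.1%.
- Difference: 41 points.

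With 550 + 200 children the shares are 47.4% and 9.5%, a difference of 38 points. With 606 + 144 (exactly 750) it is 42 points. At 25% to 45% prevalence the difference runs from about 30 to 49 points.

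**Step 4: bias of a pooled contrast.** Bias = difference in infected share × WHZ gap. With no true antibiotic effect, the false-positive rate is Φ(bias/SE − 1.96) + Φ(−bias/SE − 1.96), with SE = 0.886 × √(1/254.5 + 1/247) = 0.079.

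| Assumed WHZ gap | Bias (WHZ) | False-positive rate |
|---|---|---|
| 0.1 | about 0.04 | about 8% |
| 0.2 | about 0.08 | 16-18% |
| 0.3 | 0.11-0.13 | 30-35% |

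A gap of 0.38-0.42 gives a bias as large as the planned effect of 0.16.

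**Step 5: what the sequences with controls provide.** The information for one antibiotic versus control is the sum of n₁n₂/(n₁ + n₂) over sequences:

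- 1:1:2 sequence: 98.5 × 197/295.5 = 65.7.
- 1:1:1 sequence: 50 × 50/100 = 25.
- Detected-infection sequence: 0.

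The total is 90.7. Two arms of 250 give 125. So 90.7 equals two arms of 2 × 90.7 ≈ 181. SE = 0.886/√90.7 = 0.093, and power = Φ(0.16/0.093 − 1.96) ≈ 40%. With 550 + 200 children the equivalent is 186 per arm and power is about 41%.

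**The case against.** The strongest reply is that the analysis text is one paragraph of an article and a fuller analysis plan may exist. The multivariate model leaves its factors open, so sequence or infection status is not excluded. The t and chi-square tests are described for associations between outcomes and independent variables, not explicitly for comparing arms. This stands: a reader might infer that the protocol prescribes an unadjusted pooled test of the arms, and it does not. The confounding is therefore conditional on pooling without regard to sequence. The reply does not reach the allocation itself, which the protocol fixes. Covariate adjustment can only extrapolate to controls with detected infection, since none are randomised.

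A reader might also infer that no infected child can be a control. That is true only of detected infection. Later children are allocated 1:1:1 and samples are planned for 606 children only, so about 17 to 23 untested infected children could be expected in control. The shares above already count them.

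The size and direction of bias are not documented either. No WHZ gap is given. If infected children end lower, a real benefit would be hidden; if they end higher, the bias reverses. It would go too far to say that the trial leans towards a finding of no benefit, because Strengths and Limitations sets out both outcomes conditionally. Its subgroup sentence does not name infected children, so it needs qualifying, not deleting.

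Finally, not all 606 need enter Phase 3. Antibiotic use in the past month excludes a child, and the RCT has been delayed while phase 1 has begun. The counts are illustrations of the stated plan.

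**Conclusion.** The point holds in this form. Control allocation depends on detected infection, so a comparison of either antibiotic with control that pools the three sequences would be confounded. On the plan's 35% prevalence the arms would differ by about 38-42 percentage points in infected share (30-49 points at 25-45% prevalence). The resulting bias is about 0.04 to 0.13 WHZ for assumed gaps of 0.1 to 0.3, against a planned effect of 0.16. These figures assume that nearly all phase 1 children are randomised and that later recruits have the same prevalence.

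One conclusion needs none of these assumptions: antibiotic versus none cannot be estimated from randomised data in children with detected subclinical infection. A later analysis plan cannot change that.

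It does not follow that the whole trial is compromised. Amoxicillin versus azithromycin is 1:1 in every sequence and is unaffected. The control contrasts remain valid within the 1:1:2 and 1:1:1 sequences. No view is taken on how children with detected infection should be allocated or treated.

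**What to change.** Allocation and treatment stay as they are. Four changes of wording are needed, in the protocol and in any analysis plan:

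1. Estimate amoxicillin versus control and azithromycin versus control only in the 1:1:2 and 1:1:1 sequences, with sequence as a fixed effect.
2. Let the detected-infection sequence contribute only to amoxicillin versus azithromycin.
3. State that antibiotic versus none is not estimable in children with detected subclinical infection. Qualify the third objective and the subgroup sentence in Strengths and Limitations to match.
4. Restate power for the control contrasts: about 40-41% for 0.16 WHZ, with information equal to about 181-186 per arm, against a nominal 52% at 250 per arm.

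The cost is a lower stated information for the control contrasts and a narrower population for that claim. The RCT component is reported as delayed, so the wording can still be settled before Phase 3 data exist.
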